#### Vote of leading Ethics Committee:

Date of ethics committee application:

2019-06-04

Ethics committee number:

1651/2019

Vote of the Ethics Committee:

Approved

Date of the vote:

2019-09-19

### Statistical Plan:

We will use Multilevel Modeling (MLM) for analyzing data of the EMA study (assessing differences in event- and signal-based affective responses). The data of MLM will be fitted using lme4 package (Bates et al., 2015) and lmerTest package (Kuznetsova et al., 2017). Within-person (time) change will be depicted in level 1 and a between-person submodel in level 2, dunking how affective responses will vary between groups (NSSI vs. HC). For the Experimental Study 1 task involving NSSI-stimuli, we will perform a 2 (group NSSI vs non-NSSI patients) x 2 (stimuli quality: NSSI-related vs neutral) repeated measures ANOVA on our dependent variables (accuracy and reaction times) as well as post-experimental comparisons (e.g. NSSI urge, perceived stress). Statistical analyses for Experimental Study 2 include number of initial fixations, time of fixations, salivary cortisol, HR as well as SCR and psychological questionnaire data. Differences between socially excluded and included participants are analyzed using repeated measures Analysis of Variance (rmANOVA). A priori power analysis using G\*Power (Faul, Erdfelder, Lang, & Buchner, 2007) revealed that our study with a repeated measures design (main hypotheses) including n=50 participants per study will be efficiently powered to detect a medium effect size (i.e., interaction, Cohens  $f = 0.25$ , correlation among measurements  $r = 0.50$ ) with a power of  $1-\beta = 0.80$ . Our power calculations follow the suggestions by Cummings (2014). We expect to detect large effects (=clinically relevant) in between-subject analyses. The sample size of

$n=50$  for each study is within the recommended range of level 2 grouping variables to establish accurate estimates in multilevel-modeling (Maas & Hox, 2005) for analyzing EMA.

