### Brief summary in scientific language

**RATIONALE:** Non-suicidal self-injury (NSSI) represents a major worldwide mental health concern in adolescents. One of the underlying mechanisms of NSSI are the negative biases in processing social feedback from others. Especially the friendship groups in which peers engage in NSSI and experiences of social rejection are discussed as significant predictors for NSSI behavior. Both are prominent phenomena in digital social media, but only little is known about the triggering factors for NSSI behavior in online interactions (e.g. pictures, words, social dynamics).

**AIM:** We aim to address this paucity of research by conducting two laboratory studies and an ecological momentary assessment (EMA) over one week with an adolescent cohort. The three main objectives of this research project are (1) to investigate the purposes, risks, and benefits of social media related to NSSI in an everyday context using a 7-days real-life assessment, (2) to understand whether the presentation of wounds, scars, materials used for NSSI or words related to NSSI provoke arousal, behavioral activation or an urge or thoughts to NSSI, and (3) to explore if social exclusion alters the reactivity towards NSSI-related stimuli.

**METHOD:** The study uses EMA by means of a programmed smartphone app that allows patients to report events, affects, and experiences on a daily basis with an emphasis on social media usage and stress-related events. We will include 50 participants (n=25 patients with NSSI; n=25 healthy adolescents) in this phase of the project. Subsequently, these 50 participants will be invited to our first laboratory study using eye-tracking and psychophysiological measures during the presentation of NSSI-related stimuli to examine attentional bias, stimuli avoidance, autonomic reactivity and self-

report of perceived stress and NSSI-related cognitions. A third study will investigate the effect of social exclusion in 50 participants with a current history of NSSI on hormonal, physiological and reported subjective stress during exposure with NSSI-related material embedded in social media content.

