| 
 
• Study 1: Urge/ideation to NSSI, NSSI frequency/intensity during 7 day period (EMA)
 
• Study 2: Urge/ideation to NSSI (self-rated), initial fixation & fixation time (both eye-tracking), autonomous response (SCR, HR) during experimental procedure
 
• Study 3: Cortisol stress response, heart rate response, initial fixation & fixation time (eye-tracking) during experimental procedure.
 
 |
| Secondary Outcome:                                                                                                                                                                                                                                                                                                                                                                                                                                                  |
| 
 
• Study 1: Mood, motives for NSSI (both, self-rated; ecological momentary assessment; duration: 7 days)
 
• Study 2: stress arousal/appraisal, positive and negative affect (all, self-rated), pupil dilatation (eyetracking) during experimental procedure
 
• Study 3: fundamental basic needs, stress arousal/appraisal, urge/ideation to NSSI (all, self-rated) during experimental procedure.
 
         |

  

| Study Design    |
|-----------------|
| Purpose: |
| Other           |

|                                      |
|--------------------------------------|
| Study Type:                   |
| Non-Interventional            |
| Longitudinal/cross-sectional: |
| Cross-sectional                      |

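### The Study 2 ANOVA is planned on accuracy and reaction times, which are endpoints of no study, and four of the five declared Study 2 primary measures have no stated analysis in the protocol

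*Protocol*

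**What the plan says.** The Endpoints table gives the Study 2 primary outcomes as self-rated urge/ideation, then initial fixation and "fixation time (both eye-tracking), autonomous response (SCR, HR) during experimental procedure". The secondary outcomes are listed as "Study 2: stress arousal/appraisal, positive and negative affect (all, self-rated), pupil dilatation (eyetracking) during experimental procedure".

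The METHOD paragraph of the scientific summary describes the same study as the "first laboratory study using eye-tracking and psychophysiological measures during the presentation of NSSI-related stimuli".

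The Statistical Plan specifies for Experimental Study 1 a group x stimulus "repeated measures ANOVA on our dependent variables (accuracy and reaction times"), "as well as post-experimental comparisons (e.g. NSSI urge, perceived stress").

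On the other laboratory study it says: "Statistical analyses for Experimental Study 2 include number of initial fixations, time of fixations, salivary cortisol, HR as well as SCR" and questionnaire data. It continues: "Differences between socially excluded and included participants are analyzed using repeated measures Analysis of Variance (rmANOVA").

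**The concern.** The protocol declares one set of primary outcomes for Study 2 and fixes a different set of variables for its main model. This is a mismatch between two things the protocol states, so it is not detail that could be left to a separate analysis plan.

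The link between declared outcome and planned test is at stake. An analyst who follows the Statistical Plan literally runs the Study 2 ANOVA on two variables that are not endpoints. An analyst who follows the Endpoints table must choose the model, the contrast and the summary of each eye-tracking and autonomic measure without guidance from this document. Eye-tracking and psychophysiology are the main measurements of Study 2, so the gap falls on the central part of that study.

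**Working it through.** The point rests on comparing sections, not on a calculation.

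**Step 1: which study is which.** The Endpoints table numbers the studies 1 to 3. The Statistical Plan uses Experimental Study 1 and 2. Experimental Study 2 carries salivary cortisol and the contrast of excluded with included participants. The arm descriptions and the Endpoints table place Cyberball and cortisol only in Study 3. Hence Experimental Study 2 is Study 3, and Experimental Study 1 is Study 2.

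**Step 2: trace each Study 2 primary measure into the Statistical Plan.**

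| Study 2 primary measure (Endpoints) | Named for Experimental Study 1? | Named elsewhere in the Statistical Plan? |
|---|---|---|
| Urge/ideation | Urge only, as an example of a post-experimental comparison | No |
| Initial fixation | No | Only for Experimental Study 2 |
| Fixation time | No | Only for Experimental Study 2 |
| SCR | No | Only for Experimental Study 2 |
| HR | No | Only for Experimental Study 2 |

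Four of five have no stated analysis for Study 2. The Study 3 analysis cannot stand in for it: Study 3 compares excluded with included participants who all have NSSI, whereas Study 2 compares NSSI with healthy adolescents.

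**Step 3: trace the ANOVA variables back.** Accuracy and reaction time are not primary or secondary outcomes of Study 1, 2 or 3. They appear in the document only in this one sentence. Result: 0 of 2.

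**Step 4: is the list of variables open?** The bracket after the dependent variables has no 'e.g.', while the bracket after the post-experimental comparisons does. The first list therefore reads as a definition and the second as examples.

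**Step 5: other signs of misalignment.** The same sentence describes the comparison group as patients without NSSI, while the summaries and Arm 2 say healthy adolescents or controls. The sentence thus departs from the Study 2 design on groups as well as outcomes.

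**Side check: does the fix disturb the power statement?** The stated claim is n = 50, f = 0.25 for the interaction, r = 0.50, power 0.80. No alpha is stated, so 0.05 is assumed. With k = 2 groups and m = 2 measurements:

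- lambda = f² x N x m / (1 − r) = 0.0625 x 50 x 2 / 0.5 = 12.5
- df1 = (k − 1)(m − 1) = 1 and df2 = (N − k)(m − 1) = 48
- power = 0.934, and the smallest N for 0.80 is 34

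The stated 0.80 at n = 50 is therefore not reproduced at alpha 0.05. Power is 0.822 at alpha 0.0125 (0.05/4) and 0.799 at 0.01 (0.05/5). Under the alternative 'as in SPSS' effect-size convention it is about 0.40 at alpha 0.05, and the protocol does not say which convention was used. None of this supports or weakens the point. The power statement concerns a repeated measures interaction and names no outcome, so changing the variables leaves it as it is.

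**The case against.** **A statistical analysis plan may exist and may name the right variables.** This is true, and it limits the claim to what this protocol states. A reader might infer that the primary measures will receive no test anywhere; the document cannot show that. But the protocol does not defer the choice. It makes one, and a later plan that named fixations, SCR and HR would have to depart from it.

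**A response task may exist.** The Statistical Plan calls Experimental Study 1 a task, and the second objective includes behavioural activation, which reaction time could arguably reflect. So the inference that accuracy and reaction time are simply a mistake is not secured. They may be undeclared outcomes of an undescribed task. Even then they are not endpoints, and the declared ones remain without a model.

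**The second objective does have a planned test in part.** It asks about arousal, behavioural activation and urge or thoughts of NSSI, and urge has a loosely specified comparison. Attentional bias is mentioned in METHOD, not in that objective. It would be wrong to say the objective is left wholly untested.

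**The list for Experimental Study 2 may blend the two laboratory studies.** It includes SCR, which the Endpoints table gives for Study 2 but not for Study 3. This stands as a further inconsistency. Cortisol and the exclusion contrast still make Study 3 the better reading, and nothing in that sentence supplies a group x stimulus model for Study 2.

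**The outcomes cannot be chosen freely after the fact.** They are listed, and registration is described as prospective. This also stands. What is left open is which model and contrast apply to each listed outcome.

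**Conclusion.** The point holds as an internal contradiction. The protocol's stated Study 2 analysis does not match its declared primary outcomes: neither of the two ANOVA variables is an endpoint, four of the five primary measures have no stated analysis in the protocol, and the fifth, urge/ideation, appears only by way of example. The attentional and autonomic part of the Study 2 question therefore has no specified test.

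The conclusion rests on counting urge/ideation as one measure and on reading Experimental Study 2 as Study 3. It does not depend on the power figures or on an assumed alpha.

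It does not extend to saying that the second objective has no test, that no response task exists, or that the outcomes will go unanalysed. Because the mismatch concerns the primary outcomes of one of three studies, it should be corrected before the Study 2 data are analysed.

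**What to change.** In the Experimental Study 1 sentence of the Statistical Plan:

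1. Name initial fixation, fixation time, SCR and HR as the dependent variables of the 2 (group) x 2 (stimulus type) model, and state that the group x stimulus interaction is the test for each.
2. Name urge/ideation explicitly as a primary outcome with its own group comparison, outside the 'e.g.' list.
3. If a response task exists, describe it and list accuracy and reaction time as exploratory outcomes. If not, delete them.
4. While the sentence is open, align the comparison group with the healthy controls named elsewhere, and reconcile the place of SCR between Study 2 and Study 3.

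The cost is a wording change, with no new data and no new participants, since the test remains the interaction that the power statement already addresses. One consequence should be faced openly: with several primary tests each at an assumed 0.05, the chance of at least one false positive is 1 − 0.95⁴ = 0.185 for four and 1 − 0.95⁵ = 0.226 for five if the tests are independent. The authors should say how the set will be interpreted. The interaction power figures do not cover a between-group comparison of urge.

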**RESULTS/INNOVATION:** To our knowledge, this is the first study to investigate triggering effects of social media content in adolescents with NSSI conducting an everyday study as well as laboratory experiments. We study mechanisms that lead to NSSI using a multi-method approach including biological, behavioral and self-report measures to understand an issue that is highly relevant in clinical work.

| Health condition or problem studied             |
|-------------------------------------------------|
| Diagnosis:                               |
| Non-Suicidal Self-Injury                        |
| F60.3 Emotionally unstable personality disorder |
| Healthy volunteers:                      |
| Yes                                             |

  

| Interventions, Observational Groups                                                                                                                                                                                                                                                                                                                                                 |
|-------------------------------------------------------------------------------------------------------------------------------------------------------------------------------------------------------------------------------------------------------------------------------------------------------------------------------------------------------------------------------------|
| Arm 1:                                                                                                                                                                                                                                                                                                                                                                       |
| 
 
• Study 1: Ecological Momentary Assessment for one week with NSSI-patients.
 
• Study 2: Presenting neutral and NSSI-related stimuli for eyetracking in NSSI-patients.
 
• Study 3: Social exclusion (according to Cyberball) prior to a presentation of neutral and NSSI-related stimuli with NSSI-patients.
 
       |

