| Arm 2:                                                                                                                                                                                                                                                                                                                                                                       |
| 
 
• Study 1: Ecological Momentary Assessment for one week with healthy controls.
 
• Study 2: Presenting neutral and NSSI-related stimuli for eyetracking in healthy controls.
 
• Study 3: Social inclusion (according to Cyberball) prior to a presentation of neutral and NSSI-related stimuli with NSSI-patients.
 
 |

  

| Endpoints                                                                                                                                                                                                                                                                                                                                                                                                                                                                  |
|----------------------------------------------------------------------------------------------------------------------------------------------------------------------------------------------------------------------------------------------------------------------------------------------------------------------------------------------------------------------------------------------------------------------------------------------------------------------------|
| Primary Outcome:                                                                                                                                                                                                                                                                                                                                                                                                                                                    |

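### As written, Study 2 compares NSSI urge after the experiment, outside the group × stimulus model, so a group difference could not show that the stimuli provoked the urge

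*Protocol*

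**What the plan says.** The second objective, in the scientific summary, is causal. It asks whether wounds, scars, materials or "words related to NSSI provoke arousal, behavioral activation or an urge or thoughts to NSSI". The Endpoints table gives the primary outcomes as "Study 2: Urge/ideation to NSSI (self-rated), initial fixation & fixation time (both eye-tracking), autonomous response (SCR, HR) during experimental procedure".

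Both groups receive both kinds of material. Arm 1 reads "Study 2: Presenting neutral and NSSI-related stimuli for eyetracking in NSSI-patients" and Arm 2 reads "Study 2: Presenting neutral and NSSI-related stimuli for eyetracking in healthy controls". The sample is "n=25 patients with NSSI; n=25 healthy adolescents". The clinical group must have NSSI within the past 12 months, and controls must show no current mental disorder.

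The Statistical Plan calls this experiment Experimental Study 1. Its model crosses group with "stimuli quality: NSSI-related vs neutral) repeated measures ANOVA on our dependent variables (accuracy and reaction times". The same sentence continues with "as well as post-experimental comparisons (e.g. NSSI urge, perceived stress". The protocol mentions no pre-exposure urge rating, change score or rating by stimulus type.

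**The concern.** To show that stimuli provoke an urge, the analysis needs a contrast that the stimuli can move: NSSI-related against neutral, or after exposure against before. A single rating after a session containing both kinds of material has no stimulus level. The contrast left is patients against controls.

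The groups are not randomised and are formed on the behaviour under study, so a difference in urge before any stimulus is to be expected. A group difference after the session may be no more than that difference. The risk is that a positive result on a primary outcome is read as support for the second objective when it does not bear on it.

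**Working it through.** **1. The plan's own power figure.** The Statistical Plan states power 0.80 for an interaction with f = 0.25, r = 0.50 and N = 50. Alpha is not stated; I assume 0.05. For k = 2 groups and m = 2 conditions, the usual noncentral F calculation is:

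- λ = f² × N × m / (1 − r) = 0.0625 × 50 × 2 / 0.50 = 12.5
- df = (k − 1)(m − 1) = 1 and (N − k)(m − 1) = 48
- power = 0.93; N = 34 would give 0.80

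So N = 50 is sufficient, though it is not the N these inputs yield. The figure concerns an interaction and says nothing about a post-session group comparison.

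**2. The post-session comparison when the stimuli do nothing.** Inputs: 25 per group (protocol); two-sided alpha 0.05 (assumed); baseline gap d in SD units (assumed, shown as a range). If exposure changes nothing, the gap is still there afterwards. The two-sample t-test has 48 df and noncentrality d × √(25/2) = 3.536 × d.

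| Baseline gap d | Noncentrality | Probability of p < 0.05 |
|---|---|---|
| 0 | 0 | 0.05 |
| 0.5 | 1.77 | 0.41 |
| 0.8 | 2.83 | 0.79 |
| 1.0 | 3.54 | 0.93 |

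**3. Group × time on the same data.** With two ratings per person, this test is a two-sample t-test on the change scores, and a stable baseline gap cancels. In 10,000 simulated trials per setting (r = 0.5, no stimulus effect, no drift), the rejection rate was 0.049 to 0.052 for gaps from 0 to 1.5 SD. The post-session comparison on the same simulated data reproduced the table.

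**4. What the 0.93 means.** Under the convention in step 1, f = 0.25 puts each of the four cell effects at ±0.25 SD. The difference between groups in mean change is then 4 × 0.25 = 1.0 SD of a single rating. Power of 0.93 for urge applies to a difference of that size.

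**The case against.** The strongest objection is that a single post-session rating is an inference. The Endpoints table places urge among outcomes measured during the procedure. The METHOD summary lists self-report of perceived stress and NSSI-related cognitions among measures taken while stimuli are shown. In the Statistical Plan, the comparisons could be a further object of the ANOVA, or could mean before against after. Timing of ratings is also a detail often left to the statistical analysis plan.

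Part of this stands. A reader might infer that urge is rated once and can only ever be compared between groups; the protocol does not establish that. But the point is not a missing detail. The Statistical Plan assigns urge an analysis, describes it as post-experimental, and names other variables for the model that carries the stimulus factor. Extending the ANOVA to one post-session rating would still leave only the group effect. If earlier or per-stimulus ratings are intended, the repair is wording alone.

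A reader might also infer that a significant result is close to guaranteed. That needs a baseline gap of about 1 SD or more. At 0.5 SD the figure is 41%, and the protocol gives no urge means, SDs or scale from which to choose.

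A third inference, that controls near the floor of the scale would invalidate the ANOVA through unequal variances, is not supported. The floor is an assumption. With 25 per group and normal data, the pooled t-test had simulated error rates of 5.2%, 5.3% and 5.5% at SD ratios of 2, 4 and 10.

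**Conclusion.** The point holds as a mismatch between a stated analysis and a stated objective. As written, the post-experimental comparison of urge cannot distinguish provocation by the stimuli from a difference that existed beforehand.

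With no stimulus effect, the probability of a significant group difference runs from 5% with no baseline gap to 93% at 1.0 SD. These figures rest on 25 per group, an assumed two-sided alpha of 0.05, one post-session rating and an assumed gap. The direction of the problem follows from the design; its size cannot be fixed from the protocol. The same applies to perceived stress, a self-rating named in the same clause.

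**What to change.** In the Statistical Plan, replace the post-experimental comparison for urge/ideation and perceived stress with one of the following, and state when the ratings are taken:

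- a group × time test on a rating before and a rating after exposure, keeping both groups; or
- a group × stimulus test, if ratings are taken separately after NSSI-related and after neutral stimuli.

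Both are interactions of the kind the plan already powers. The first costs at most one brief added self-rating. It does not separate NSSI-related from neutral material, and it cancels session drift only where the drift is common to both groups. The second answers the objective more directly, but is cheap only if the presentation already allows separate ratings; the protocol does not describe blocked presentation.

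A before–after test in the 25 patients alone is not a good substitute. It attributes to the stimuli any change due to time, laboratory stress or repeated questioning: a drift of 0.3 or 0.5 SD of the change score would be significant 30% or 67% of the time. It also gives up the group interaction.

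The same sentence calls the comparison group non-NSSI patients, whereas both summaries and the description of Arm 2 have healthy adolescents or controls. These should be reconciled.

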#### Recruitment Locations

- Recruitment countries: Austria
- Number of study centers: Monocenter study
- Recruitment location(s): University Medical Center : Universitätsklinikum für Kinder- & Jugendpsychiatrie, Wien Wien
- Planned study start date: 2022-05-01
- Actual study start date: 2022-06-01
- Target Sample Size: 50 per study
- Final Sample Size: No Entry

| Inclusion Criteria                                                                                                                                                                                                                                                                                                                                      |
|---------------------------------------------------------------------------------------------------------------------------------------------------------------------------------------------------------------------------------------------------------------------------------------------------------------------------------------------------------|
| Sex: All                                                                                                                                                                                                                                                                                                                                         |
| Minimum Age: 14 Years                                                                                                                                                                                                                                                                                                                            |
| Maximum Age: 18 Years                                                                                                                                                                                                                                                                                                                            |
| Additional Inclusion Criteria:
Inclusion criteria for the clinical group are (a) good German language skills, (b) fulfilling NSSI within the past 12 month after SITBI-G, (c) aged between 14;00 and 17;11 years. Inclusion criteria for the healthy controls are (a) good German language skills and (b) aged between 14;00 and 17;11 years. |

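### Study 3 fixes repeated measures ANOVA, which drops a participant from an outcome when one repeated value of it is missing; a linear mixed model would keep the remaining values

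*Protocol*

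**What the plan says.** The Statistical Plan names a method for each of the three studies.

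- **EMA study:** multilevel models. "The data of MLM will be fitted using lme4 package", together with lmerTest.
- **Experimental Study 1** (Study 2 in the Endpoints table): a 2 x 2 repeated measures ANOVA, group by stimulus type.
- **Experimental Study 2** (Study 3 in the Endpoints table): "Statistical analyses for Experimental Study 2 include number of initial fixations, time of fixations, salivary cortisol, HR as well as SCR" and questionnaire data. The method is fixed: "Differences between socially excluded and included participants are analyzed using repeated measures Analysis of Variance (rmANOVA").

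The Endpoints table lists as primary "Study 3: Cortisol stress response, heart rate response, initial fixation" and fixation time. Under Recruitment Locations the size is given as "Target Sample Size: 50 per study". The Statistical Plan calls 50 participants "efficiently powered to detect a medium effect size (i.e., interaction, Cohens" f of 0.25, with a "correlation among measurements" of 0.50 and "with a power of" 0.80.

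The protocol does not state alpha, the number of saliva or heart rate measurements, the allocation ratio in Study 3, or an allowance for loss.

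**The concern.** A cortisol response is measured as a series of samples. Classical rmANOVA uses only participants whose series is complete. One unusable sample removes the person from the cortisol analysis and discards that person's valid samples as well. Two things are at stake.

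- **Power.** The share of complete participants shrinks with every added measurement, and the planned 50 shows no margin for this.
- **Validity.** Analysing only complete cases is generally unbiased only if loss is unrelated to condition and to the measured values. The manipulation here is social exclusion of adolescents with NSSI, so loss related to condition cannot be ruled out beforehand.

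A linear mixed model with the same fixed effects uses every observed value and needs only the weaker assumption of missing at random. The project already plans such models for the EMA data.

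**Working it through.** **Inputs.** From the Statistical Plan: N = 50, f = 0.25, r = 0.50, power 0.80. Assumed, because not stated: alpha 0.05, two equal groups in Study 3, m = 2 to 6 repeated measurements, and independent loss per measurement of 3% to 20%.

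**1. The plan's own figure.** For the group-by-time interaction with two groups, take λ = f²·N·m/(1 − r), df1 = m − 1 and df2 = (N − 2)(m − 1). With m = 2, λ = 0.0625 × 50 × 2/0.5 = 12.5 on 1 and 48 df, and power is 0.934. A power of 0.80 is reached under other unstated settings:
- alpha 0.01 with m = 2 gives 0.799;
- the Cohen effect-size option, λ = f²·N·(m − 1), gives 0.810 with m = 5.

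The stated figure therefore cannot be reproduced from the document alone, but it cannot be called wrong.

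**2. Complete participants.** The expected number is 50 × (1 − p)^m. For m = 5:
- 3% loss: 0.97^5 = 0.859, so 42.9
- 5% loss: 0.95^5 = 0.774, so 38.7
- 10% loss: 0.90^5 = 0.590, so 29.5
- 20% loss: 0.80^5 = 0.328, so 16.4

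**3. Complete-case power.** Put these numbers into the first formula with alpha 0.05. For m = 5 and 10% loss, λ = 0.0625 × 29.5 × 5/0.5 = 18.4 on 4 and 27.5 × 4 = 110 df, and power is 0.939. Each cell shows expected completers, then power.

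| m | 5% loss | 10% loss | 20% loss |
|---|---|---|---|
| 2 | 45.1; 0.907 | 40.5; 0.873 | 32.0; 0.781 |
| 4 | 40.7; 0.973 | 32.8; 0.930 | 20.5; 0.739 |
| 5 | 38.7; 0.984 | 29.5; 0.939 | 16.4; 0.687 |
| 6 | 36.8; 0.990 | 26.6; 0.942 | 13.1; 0.619 |

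Power stays above 0.80 up to 10% loss and is below it at 20%.

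**4. Comparison with a mixed model.** Simulation with 1,500 runs per setting, N = 50, compound symmetry with r = 0.50, f = 0.25, and values missing completely at random. The mixed model is a random-intercept model fitted by REML with the same fixed effects.

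| m | Loss | rmANOVA, complete cases | Mixed model |
|---|---|---|---|
| 2 | 5% | 0.913 | 0.925 |
| 2 | 10% | 0.863 | 0.881 |
| 2 | 20% | 0.760 | 0.817 |
| 6 | 5% | 0.987 | 0.999 |
| 6 | 10% | 0.920 | 0.994 |
| 6 | 20% | 0.575 | 0.994 |

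Type I error was 0.042 to 0.056 for both methods.

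**5. Loss that depends on condition and the first value.** Under a deliberately strong assumed mechanism, in which later values are lost depending on group and the first observed value, complete-case type I error was 0.07 to 0.12 for m = 2 and 0.13 to 0.28 for m = 6. The mixed model gave 0.05 to 0.06.

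**The case against.** The strongest reply is that the document contains no error. It names a standard method, it does not prescribe listwise deletion, and rules for missing values may stand in a statistical analysis plan that is not shown. With complete, balanced data under compound symmetry the two methods agree. Much of this stands: the lack of a missing-data rule is not a finding. The choice of rmANOVA is in the protocol, however, and that choice is the point.

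Some stronger readings are tempting but not supported.

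- **That ordinary loss undoes the power claim.** A reader might set the roughly 30 completers at 10% loss against the 34 participants that give 0.80 power in step 1's formula. The 30 belongs to five measurements and the 34 to two. Within one design, complete-case power at 10% loss is 0.87 to 0.94 for 2 to 6 measurements.
- **That a missing saliva sample removes the person from everything.** Deletion is per outcome; heart rate and eye-tracking are unaffected. If fixations or heart rate are averaged per condition, which the protocol does not say, a lost trial need not drop anyone.
- **That the mixed model costs nothing.** It needs a covariance structure, a small-sample degrees-of-freedom method and missing at random. It cannot recover a participant with no value on an outcome. The simulation used the correct covariance form; an unstructured covariance estimated from about 50 people was not tested.
- **That both laboratory experiments need the change.** Experimental Study 1 has two stimulus types. With two measurements the gain is about 1 to 2 power points at 5 to 10% loss.

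**Conclusion.** The point holds as a cheap improvement to Study 3, above all for cortisol. The fixed method discards usable data when a series is incomplete and relies on a stronger missing-data assumption than necessary. Its practical size is not known from the document. With two measurements and modest loss it is small. It becomes large with many measurements and heavy loss: 0.575 against 0.994 at six measurements and 20%. The risk to type I error in step 5 shows what can happen under a strong assumed mechanism; it does not predict what this trial will see.

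The finding that power stays above 0.80 up to 10% loss depends on alpha 0.05, the first formula in step 1, and f = 0.25 held constant whatever the number of measurements. Under the settings in step 1 that start at about 0.80, there is little or no reserve for loss. The document does not say which settings were used, so neither a shortfall nor a safe margin can be claimed.

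**What to change.** In the Statistical Plan, replace rmANOVA for the repeated outcomes of Experimental Study 2 (Study 3) with a linear mixed model:

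- fixed effects for condition, time and their interaction for cortisol and other series, or condition, stimulus type and their interaction for outcomes measured per stimulus type;
- a participant random effect, with the covariance structure named in advance;
- all available observations included;
- a small-sample degrees-of-freedom method, such as Kenward-Roger or Satterthwaite, named in advance;
- complete-case rmANOVA kept as a sensitivity analysis, with the number of complete participants reported per outcome.

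For the 2 x 2 Experimental Study 1 the same change is optional.

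The cost is a change of wording and two advance decisions, on covariance and degrees of freedom. No further participants, visits or samples are needed, and the project already uses mixed-model software. The remaining price is reliance on missing at random, which should be stated.
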